#### Methods of statistical analyses

The modified intent-to-treat (mITT) analysis set will be considered as the full analysis set. This will include all evaluable patients: ie, all randomized patients who receive at least one treatment and who have a score at randomization and at least one post-randomization ACT total score. The mITT analysis set will be used for efficacy analyses. Missing data will be replaced according to the principle of LOCF (the last observation carried forward). The per-protocol (PP) analysis set will include only those mITT patients who have no significant protocol deviations and who received the treatment to which they were randomized. Analysis of primary efficacy endpoint will be repeated on the PP analysis set to test for robustness of results. All the randomized patients who receive at least one treatment and for whom any post-baseline safety data are available will be included in the safety analysis set. The safety analysis set will be used to assess safety variables.

In general, all efficacy and safety variables will be summarized using descriptive statistics and graphs as appropriate. Continuous variables will be summarized by descriptive statistics (sample size (*n*), mean, standard deviation (SD), minimum, median and maximum). Categorical variables will be summarized in frequency tables (frequencies and percentages). The primary efficacy variable, the change from baseline in ACT total score to the end of treatment period will be analyzed using an analysis of covariance (ANCOVA). The ANCOVA analysis will include the baseline ACT total score as covariate, treatment as a fixed effect and center as a random effect. Secondary endpoints will be analyzed using a *t* test or Wilcoxon rank sum test as appropriate. All analyses will be performed using SAS software, version 9.3 (SAS Inc., Cary NC, USA). All statistical tests will be conducted at a 2-tailed significance level of 5 %.

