### Interventions

Acupuncture will be performed by senior attending doctors at 12 clinical centers. Asthmatic patients randomly allocated will receive verum/sham acupuncture once every other day with a total of 20 treatment sessions in 6 weeks and 3 months follow-up (see Fig. 1). Patients are required to complete case report form (CRF), asthma quality of life questionnaire (AQLQ) and record daily asthma symptom scores, acute asthma episodes and the use of as-needed salbutamol aerosol and/or prednisone tablets in the asthma diary from the completion of screening test to the end of the follow-up visits. Salbutamol aerosol (100 μg/puff) will be taken as needed for asthma attack. If the symptoms are still not controlled within a maximum safe dose, prednisone tablets will be suggested to take at a dose of 20 mg each day for 3–5 days. Patients should record use of salbutamol aerosol and/or prednisone tablets in the asthma diary.

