#### Secondary outcome measurements

Percentage of symptom-free days (SFDs) [30];Average dosages of salbutamol aerosol and/or prednisone tablets [31, 32];Lung functions assessed by FEV_1_ and mean morning and evening PEF [33, 34];Daily asthma symptom scores [35];AQLQ [36];Peripheral blood eosinophil (EOS) counts;Number of asthma exacerbations.

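### Membership of the only efficacy set depends on a post-randomization ACT score, so diary-based secondary outcomes recorded in treated patients who leave before a repeat ACT are left out of the efficacy analyses.

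*Protocol article*

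**What the plan says.** The rule is in the protocol article under Methods of statistical analyses. The modified intent-to-treat (mITT) set, which serves as the full analysis set, consists of "all randomized patients who receive at least one treatment and who have a score at randomization and at least one post-randomization ACT total score". Its use is then fixed: "The mITT analysis set will be used for efficacy analyses". Nothing limits that sentence to the ACT.

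The same section defines two other sets. The per-protocol set is a subset of the mITT set and serves the primary endpoint only: "Analysis of primary efficacy endpoint will be repeated on the PP analysis set to test for robustness of results". The safety set requires one treatment and some post-baseline safety data but no ACT, and it is assigned to safety variables.

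Secondary outcome measurements lists symptom-free days, rescue medication dosage, daily symptom scores and "Number of asthma exacerbations", among others. Under Interventions, patients note symptom scores, acute episodes and rescue use "in the asthma diary from the completion of screening test to the end of the follow-up visits".

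**The concern.** One questionnaire decides who counts for every efficacy endpoint, including endpoints that do not use it. A patient may be randomized, treated, keep a diary for some weeks and then leave before a repeat ACT. That patient has outcome data on symptoms, rescue use and acute episodes, yet the stated rule excludes the patient from those analyses.

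This is separate from how a missing ACT is imputed. Last observation carried forward works inside the mITT set and cannot bring back a patient who is outside it. A better method for missing ACT scores would leave the problem untouched.

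Early departure is plausibly related to worsening. Under Exclusion criteria, only patients able to stop inhaled corticosteroids and other listed asthma drugs can take part, so participants rely on as-needed medication. Under Safety evaluation, the intervention stops if a serious adverse event occurs. The exacerbation and rescue endpoints could therefore be computed after removing patients selected partly on those same outcomes.

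**Working it through.** **Step 1: is there a wider set for the secondary endpoints?**

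| Set | Needs a post-randomization ACT? | Used for |
|---|---|---|
| mITT | Yes | Efficacy analyses, without limit |
| Per-protocol | Yes (subset of mITT) | Primary endpoint only |
| Safety | No | Safety variables |

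No set that is free of the ACT condition is assigned to any efficacy endpoint.

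**Step 2: can data exist without an ACT?** Yes, for the diary items, because the diary runs from screening to the end of follow-up. The only post-randomization ACT time the article names is the end of the treatment period, in the definition of the primary variable. The Follow-up section names the case report form, the AQLQ and lung function, but not the ACT. If no earlier ACT is taken, the group at risk is everyone who leaves during the 6 treatment weeks without one. If there is an earlier ACT, the group is smaller.

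**Step 3: how many patients?** Sample size gives 86 needed and 100 enrolled per arm.

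- Implied allowance: 1 − 86/100 = 0.14, or 14 per arm. Check: 86/(1 − 0.14) = 100.
- The allowance covers all dropout, and only those leaving before a repeat ACT are affected. The range is therefore 0 to about 14 per arm, if losses match the allowance.

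**Step 4: what could it do to an endpoint?** The article gives no event rates, so all rates here are assumed. Let *d* be the fraction removed in an arm, *m*₁ the mean count in those kept and *m*₂ the mean count in those removed.

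- Mean in all treated patients: (1 − *d*)·*m*₁ + *d*·*m*₂
- Mean in the ACT-conditioned set: *m*₁
- If *m*₁ and *m*₂ are the same in both arms, the difference that is hidden is (*d*_sham − *d*_verum)·(*m*₂ − *m*₁).

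Unequal loss within the allowance, with 4 verum and 14 sham removed, *m*₁ = 0.5 and *m*₂ = 1.5:

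- Verum: 0.96 × 0.5 + 0.04 × 1.5 = 0.48 + 0.06 = 0.54
- Sham: 0.86 × 0.5 + 0.14 × 1.5 = 0.43 + 0.21 = 0.64
- ACT-conditioned: 0.50 in both arms
- Hidden difference: 0.64 − 0.54 = 0.10, which agrees with (0.14 − 0.04) × (1.5 − 0.5) = 0.10

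Equal loss, 14 removed in each arm, same means:

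- All treated: 0.64 in both arms. ACT-conditioned: 0.50 in both arms.
- The difference is 0 either way. Only the level moves: (0.64 − 0.50)/0.64 = 22% too low.

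The same check on the proportion with an exacerbation assumes 20% in those kept, and 4 verum and 14 sham removed:

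- 50% in those removed: verum (96 × 0.2 + 4 × 0.5)/100 = 21.2%; sham (86 × 0.2 + 14 × 0.5)/100 = 24.2%; difference 3 points.
- 80% in those removed: verum 22.4%; sham 28.4%; difference 6 points.
- ACT-conditioned difference: 0 in both cases.

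**Step 5: how demanding are the assumed counts?** If the first repeat ACT is no later than the end of treatment, those removed contribute at most about 6 weeks. If exacerbations are counted over 6 weeks, 1.5 against 0.5 is at least a 3-fold weekly rate. If they are counted over treatment plus 3 months (about 6 + 13 = 19 weeks), it is about (1.5/6)/(0.5/19) = 9.5-fold. The counting window is not stated. The illustration therefore shows the mechanism and is not a forecast.

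**The case against.** The strongest reply is that the effect may be negligible. Fourteen per arm is a ceiling for all dropout, and the number who leave before any repeat ACT could be close to zero. Patients are blinded, and both arms receive the same needles and manipulation, so nothing in the article points to a marked imbalance in early loss. This stands, and it limits the size of the point, but it does not supply a wider analysis set.

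Four stronger readings are tempting and are not supported:

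- A reader might infer that the secondary comparisons are biased. The article does not show this. With equal loss and equal outcomes among those lost, the between-arm difference is unchanged. Understatement of the level also depends on leavers being worse, which is plausible but assumed.
- A reader might infer that these patients' events vanish from the report. They do not. Any adverse event goes into the case report form whatever its cause, and the safety set needs no ACT. What is lost is their place in the efficacy outcomes.
- A reader might extend the point to peak flow. The Procedure section describes training and recording in the baseline week, before randomization, and does not establish post-randomization peak-flow data in early leavers.
- A reader might assume that every early leaver's diary reaches the database. The article does not say when diaries are collected, so this is likely for some but not established for all.

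A further objection concerns the remedy. Adding patients with a few diary days to an unadjusted *t* test or Wilcoxon test on raw counts could make short exposure look like few events. This also stands, and the fix has to deal with it.

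**Conclusion.** The point holds in limited form. The article fixes a rule that excludes recorded, diary-based secondary efficacy data because a different instrument is missing. This is not a detail left to an analysis plan that is not shown, since both the set definition and its use are stated.

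The number removed is 0 to about 14 per arm if losses match the allowance, and it cannot be narrowed without the ACT schedule. Bias in the comparison requires early loss, or outcome among those lost, to differ between arms. Under the assumed rates a difference of 0.10 exacerbations per patient, or 3 to 6 percentage points in the proportion affected, would appear as zero. Under equal loss and equal outcomes only the level changes. The primary ACT analysis is not at issue. The change is worth making because the condition serves no purpose for these endpoints and is cheap to remove.

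**What to change.** 1. Apply the post-randomization ACT condition to the ACT endpoint only.
2. Analyze each other efficacy endpoint by randomized arm, in all randomized patients with any post-randomization record of that endpoint.
3. Express diary endpoints per day observed. Analyze exacerbations as a rate per observed time, for example with a count model that has log observed time as offset, so that a short record is not read as few events.
4. Report, by arm, how many patients the ACT condition would have removed.

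No new data collection is needed. The cost is a revised set definition and a stated rule for unequal exposure in place of a plain two-sample test on exacerbation counts. Patient numbers will differ by endpoint in the tables, and short records will give imprecise individual values. Requiring some record of the endpoint is still a selection after randomization, but a narrower one that discards no observed data on that endpoint.

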#### Follow-up

Follow-up assessments will be conducted at a clinic visit once every month and last for 3 months. Patients are required to complete the CRF, AQLQ and assess lung functions. To encourage participant compliance, we will show special solicitude for every participant and closely monitor the evolution of their illness.

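### The LOCF rule does not stop at the end of treatment, so a comparison at a follow-up visit can use on-treatment values as if they were off-treatment results

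*Protocol article*

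**What the plan says.** All of the following is in the Protocol article.

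- **Missing-data rule** (Methods of statistical analyses): after the sentence "The mITT analysis set will be used for efficacy analyses", the plan continues "Missing data will be replaced according to the principle of LOCF". No endpoint, visit or period is excepted. To enter the mITT set, a patient needs one treatment, a score at randomization and one later ACT score.
- **Primary endpoint** (same section): "the change from baseline in ACT total score to the end of treatment period".
- **Secondary endpoints** (same section): a t test or Wilcoxon rank sum test, with no time point named.
- **Schedule** (Interventions): "once every other day with a total of 20 treatment sessions in 6 weeks and 3 months follow-up". The asthma diary runs to the end of follow-up. No acupuncture is described for the follow-up months.
- **Follow-up visits** (Follow-up): "Follow-up assessments will be conducted at a clinic visit once every month and last for 3 months", and at these visits "Patients are required to complete the CRF, AQLQ and assess lung functions". AQLQ and lung function are listed secondary outcomes.
- **Robustness check** (Methods of statistical analyses): the primary endpoint is repeated on the per-protocol set. No check of LOCF or of the follow-up results is stated.

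**The concern.** LOCF assumes that the last value seen stands for the value that was missed. Between the end of treatment and a follow-up visit that assumption changes character, because the earlier value was measured under acupuncture and the later visit measures the patient without it. A patient who finishes treatment and attends no follow-up visit would receive an on-treatment value at months 1, 2 and 3. So would a patient lost during treatment.

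This differs from the usual worry about informative dropout. The substitution distorts the comparison even if follow-up data are missing completely at random and equally in both arms, a situation in which the observed values alone would give an unbiased answer.

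At stake is any statement about whether a benefit lasts once treatment ends. If verum is better at the end of treatment and the advantage then fades, part of the earlier difference is carried into each follow-up comparison. The per-protocol repeat covers only the primary endpoint and could not reveal this.

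**Working it through.** **Inputs from the article (Sample size):** ACT improvement 3.5 (verum) and 1.6 (sham), so a difference of 1.9; power 0.80; two-sided alpha 0.05; 86 per group, raised to 100 for dropout. **Not given:** the SD, the effect on AQLQ or lung function, and the missingness at follow-up.

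**Step 1. The plan's own figure.** Without an SD, 86 cannot be reproduced independently; it can only be solved backwards:

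SD = 1.9 / [(1.960 + 0.842) × √(2/86)] = 4.45 (4.42 with a t test).

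The standardized effect is 1.9 / 4.45 = 0.43. The result is sensitive to the SD: 4.0 would need 70 per group and 5.0 would need 109. The step from 86 to 100 corresponds to an allowance of 1 − 86/100 = 14%.

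**Step 2. Shift caused by the rule.** Let the true mean change at follow-up be μ in both arms (no true difference). Let shares m_v (verum) and m_s (sham) carry an end-of-treatment value. The expected difference after LOCF is

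m_v × (3.5 − μ) − m_s × (1.6 − μ).

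With equal shares m this becomes m × 1.9, whatever μ is.

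**Step 3. Error rate with equal shares.** The standard error at 100 per arm is 4.45 × √(2/100) = 0.629. The two-sided rejection rate is 1 − Φ(1.96 − shift/0.629) + Φ(−1.96 − shift/0.629).

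| m in each arm | Shift, ACT points | Shift, SD | Two-sided error | Of which favours verum |
|---|---|---|---|---|
| 5% | 0.10 | 0.02 | 5.3% | 3.5% |
| 10% | 0.19 | 0.04 | 6.1% | 4.9% |
| 14% | 0.27 | 0.06 | 7.1% | 6.2% |
| 20% | 0.38 | 0.09 | 9.3% | 8.8% |
| 30% | 0.57 | 0.13 | 14.8% | 14.6% |

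The nominal values are 5% in total and 2.5% in favour of verum. A simulation with t tests (20,000 runs) agrees: 7.1% at 14%, 9.1% at 20%, and 13.9% to 14.8% at 30%, depending on the follow-up mean assumed.

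**Step 4. Unequal shares, both arms back to baseline (μ = 0).**

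- Verum 20%, sham 8%: 0.20 × 3.5 − 0.08 × 1.6 = +0.57 points. Simulated error 14.6%.
- Verum 8%, sham 20%: 0.08 × 3.5 − 0.20 × 1.6 = −0.04 points. Simulated error 5.2%.
- Verum 5%, sham 25%: 0.05 × 3.5 − 0.25 × 1.6 = −0.23 points. The sign is reversed.

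The reversal needs the sham gain to fade too. If both arms settle at the sham level (μ = 1.6), the sham term is zero and the shift is m_v × 1.9, in favour of verum.

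**The case against.** The strongest objection is that the affected analysis is not written down. No section specifies a between-group test at month 1, 2 or 3, and visit-level detail on secondary outcomes is commonly left to a fuller plan. This stands as a condition on the point. It does not remove it: the LOCF sentence is a rule the article does fix, it follows directly on the assignment of the mITT set to efficacy analyses, and secondary outcomes are collected monthly off treatment.

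The size can also be challenged, with good reason:

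- The ACT planning effect stands in for AQLQ, lung function and diary outcomes, for which the article gives no effect. ACT is not named among the follow-up measurements, although the CRF may contain it.
- Complete loss of the difference is the extreme case. Partial fading gives a smaller shift.
- Only patients last seen on treatment matter. Someone seen at month 1 and missing later carries an off-treatment value. If half of a 14% loss were of that kind, m would be 7%, the shift 0.13 points and the error about 5.5%.

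A reader might infer more than the article supports, in four ways:

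- **That the direction is always towards persistence.** Step 4 shows that it need not be.
- **That 14% is the expected loss at follow-up.** That allowance belongs to the sample size for the ACT comparison, whose endpoint is read at the end of treatment. It is not split between treatment and follow-up.
- **That persistence is the declared purpose of follow-up.** No purpose is stated; the aims speak of efficacy. Durability is a reasonable inference and no more.
- **That the primary result is compromised.** It is read at the end of treatment, before any off-treatment visit.

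Finally, it can be said that one barring sentence is enough and that prescribing a model is preference. The sentence is indeed the essential part, but once carry-forward is barred, some other handling of missing follow-up values has to be named.

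**Conclusion.** The point holds in conditional form. As written, LOCF extends past the end of treatment, and if secondary outcomes are compared between groups at the monthly follow-up visits, on-treatment values enter off-treatment comparisons. With a fading benefit and similar missingness, the comparison is biased towards a lasting effect. With clearly more sham patients missing, the bias may disappear or reverse. So the rule can show persistence that did not occur; the article does not support saying that it will.

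The size is modest at low missingness (error 5.3% to 6.1% when 5% to 10% of each arm carry an on-treatment value) and becomes material at 20% to 30% (9.3% to about 15%). These figures rest on a back-solved SD, the ACT effect as a stand-in, no true difference at follow-up, 100 per arm and assumed carry-forward shares. They illustrate and do not forecast. The matter is confined to secondary outcomes. It should be corrected because the correction is cheap and no stated check would expose the problem.

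**What to change.** In Methods of statistical analyses, after the LOCF sentence, state that no value observed during the treatment period is carried into a follow-up visit.

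For the follow-up visits, name an analysis of the observed data: a likelihood-based repeated-measures model that includes the end-of-treatment (week-6) value, or multiple imputation by arm using the end-of-treatment value and the available follow-up values. If an LOCF result at follow-up is shown at all, label it a sensitivity analysis and report the number of carried-forward values per arm and visit.

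The cost is plan wording and one extra model. No new data are needed, and the sample size and the primary end-of-treatment analysis do not change. The downside is somewhat wider intervals at follow-up, because the estimates rest on fewer observed values. If follow-up missingness is unrelated to outcome, the spurious difference is then zero and the two-sided error returns to 5%.

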## Background

Asthma is a noninfectious chronic disease that affects as many as 334 million people of all ages in all parts of the world [1]. The World Health Organization (WHO) has estimated that 15 million disability-adjusted life-years are lost and 250,000 asthma deaths occur around the world annually [2, 3]. Asthma is now recognized as a disease of major public health importance due to its constantly increasing prevalence, morbidity, and mortality in recent decades [2, 4].

Asthma is characterized by variable symptoms of wheeze, shortness of breath, chest tightness and/or cough, and variable expiratory airflow limitations [5]. Inhaled corticosteroids (ICS) are used as first line therapy for asthma [6]; however, a significant proportion of patients remained nonadherent to corticosteroid therapy [7]. Bronchodilators are predominant medications to treat asthma [8], but controversy exists about the risks and benefits in the application of bronchodilator drugs, such as long-acting beta-agonists [9, 10]. Regarding the potential side effects of the long-term use of conventional drugs, an effective, low-risk, and non-drug strategy would provide a valuable and adjunctive treatment in asthma management [11].

As one of the most important complementary and alternative therapies, acupuncture has been used to treat a variety of diseases for more than 2000 years [12]. The WHO listed asthma and other 42 indications for acupuncture in 1979 [13] and classified the diseases treated by acupuncture into 4 categories, 107 illnesses in 2002, including asthma [14]. The National Institutes of Health (NIH) recommended acupuncture as an adjunctive treatment in comprehensive management programs of addiction, stroke rehabilitation, asthma, etc. [12, 15]. The British Thoracic Society suggested that health care professionals should be aware of the common use of complementary and alternative medicine in asthma treatment, including acupuncture [16]. Previous studies suggested that acupuncture was effective in alleviating asthmatic symptoms and could be used as an adjunct to the conventional medical management of asthma [17]. Acupuncture also improved lung function and decreased medication dosages [18]. Our previous clinical study found that acupuncture reduced the degree and frequency of exacerbations in patients with asthma [19] and had regulatory effects on mucosal and cellular immunity in patients with allergic asthma [20].

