#### Exclusion criteria

Participants meeting any of the following criteria will be excluded:Participation in another clinical trial in the previous 1 month;Have received systemic corticosteroids in the previous 2 weeks;With systemic infection, respiratory infection, pulmonary tuberculosis and fungal infection in the previous 1 month;Hospitalization due to acute exacerbation of asthma in the previous 3 months or in the baseline period;Cannot stop using inhaled corticosteroids, theophylline, long-term β_2_ agonist, sodium cromoglicate, leukotriene antagonists, anticholinergic drugs or be allergic to albuterol and corticosteroids;Complicated with other severe primary diseases (including hypertension, cancer, hyperthyroidism, bronchiectasis, cardiac insufficiency) and conditions that would prevent participation in the trial or put the participant at risk;Women who are known to be pregnant or breastfeeding;Acupuncture contraindications, such as serious atopic or infectious dermatopathy and hemorrhagic diseases (including thrombocytopenic purpura and hemophilia).

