### Procedure

An independent receptionist will initially assess each potential participant according to the inclusion and exclusion criteria. After confirmation of asthma diagnosis, participants will enter a baseline period of 1 week without treatment, during which they will be trained to use a peak flow meter, record peak expiratory flow (PEF) and maintain an asthma diary.

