### Randomization

After the completion of the baseline evaluation, eligible participants will be randomly classified into two groups: the verum acupuncture plus as-needed salbutamol aerosol and/or prednisone tablets group, the sham acupuncture plus as-needed salbutamol aerosol and/or prednisone tablets group. A computer-generated, blocked random allocation sequence will be performed by Drug And Statistics software 3.2.1 [26]. The receptionist who is not involved with data collection will provide the random number and group assignment immediately by using opaque, sealed envelopes. This procedure guarantees that randomization concealment is adequate, and will not be influenced by the acupuncture doctor or participants.

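### The primary ANCOVA has no term for prior controller use, which costs some precision and leaves chance imbalance unadjusted; within-arm ACT changes may include withdrawal drift

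*Protocol article*

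**What the plan says.** The Exclusion criteria of the protocol article rule out patients who "Cannot stop using inhaled corticosteroids, theophylline, long-term β_2_ agonist, sodium cromoglicate, leukotriene antagonists, anticholinergic drugs". A controller user who can stop is therefore eligible. Nothing in the Inclusion criteria requires prior controller use, so a patient who took none is eligible too. The Background states that "Inhaled corticosteroids (ICS) are used as first line therapy for asthma", so prior users are unlikely to be rare, but no share is given.

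The only drug-free interval with a length in the Exclusion criteria concerns another drug class: "Have received systemic corticosteroids in the previous 2 weeks". Under Procedure, "participants will enter a baseline period of 1 week without treatment". Under Randomization, "After the completion of the baseline evaluation, eligible participants will be randomly classified into two groups", and "A computer-generated, blocked random allocation sequence will be performed by Drug And Statistics software 3.2.1"; no stratification by prior controller use is described. Interventions gives both arms the same as-needed salbutamol and/or prednisone.

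Methods of statistical analyses defines the primary variable as change in ACT from baseline to the end of treatment and lists the model terms: "The ANCOVA analysis will include the baseline ACT total score as covariate, treatment as a fixed effect and center as a random effect".

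**The concern.** Take two patients with the same baseline ACT. One stopped a controller shortly before the baseline week, so the score may still owe something to that drug and the next 6 weeks may include its loss. The other never took a controller and has no such loss ahead. Baseline ACT is the only patient-level covariate in the model, and it cannot tell them apart.

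Three things follow if withdrawal does shift ACT:

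- The drift enters the residual variance, although a known baseline factor could remove it.
- A chance difference between arms in the share of withdrawn patients stays in the realised estimate.
- The mean change within each arm depends on the mix of withdrawn and never-treated patients, so it is not a clean measure of response to either needling procedure.

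The factor is known before allocation, because the controller criterion cannot be applied without asking about controller use.

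**Working it through.** **Inputs from the article (Sample size).** Anticipated improvement 3.5 (verum) and 1.6 (sham), so the difference is 1.9; two-sided α 0.05; power 0.80; 86 per group, 100 enrolled.

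**Inputs assumed.** Share of patients withdrawn from a controller, p = 0.3 to 0.7. Drop in their 6-week ACT change, d = 1 to 3 points. The article gives neither.

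**Step 1: the article's own figure.** No SD is stated, so 86 cannot be reproduced independently. Solving backwards:

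SD = 1.9 × √(86/2) / (1.960 + 0.842) = 4.45.

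The step from 86 to 100 matches 14% dropout (86/0.86 = 100).

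**Step 2: power.** An omitted yes/no factor adds p(1−p)d² to the residual variance. Case A takes 4.45 as the SD without drift, so omission increases it. Case B takes 4.45 as already containing the drift, so adjustment reduces it. Power is at 86 per arm by the normal approximation. The last column is the shift in the verum-sham difference from a 1-SD chance imbalance, d × √(2p(1−p)/86).

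| p | d | p(1−p)d² | A: SD, term omitted | A: power | A: n per arm for 80% | B: SD, term added | B: power | 1-SD shift |
|---|---|---|---|---|---|---|---|---|
| 0.3 or 0.7 | 1 | 0.21 | 4.47 | 79.6% | 87 | 4.42 | 80.4% | 0.07 |
| 0.3 or 0.7 | 2 | 0.84 | 4.54 | 78.3% | 90 | 4.35 | 81.7% | 0.14 |
| 0.3 or 0.7 | 3 | 1.89 | 4.65 | 76.3% | 95 | 4.23 | 83.8% | 0.21 |
| 0.5 | 1 | 0.25 | 4.48 | 79.5% | 88 | 4.42 | 80.5% | 0.08 |
| 0.5 | 2 | 1.00 | 4.56 | 78.0% | 91 | 4.33 | 82.0% | 0.15 |
| 0.5 | 3 | 2.25 | 4.69 | 75.6% | 96 | 4.19 | 84.5% | 0.23 |

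Omission therefore costs 80 − 79.6 = 0.4 to 80 − 75.6 = 4.4 points of power in case A.

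**Step 3: chance imbalance in proportion.** The standard error of the difference at 86 per arm is 4.45 × √(2/86) = 0.68. A 1-SD imbalance of 0.07 to 0.23 points is about 10% to 34% of that. Squared, this is about 1% to 11%, the same share that p(1−p)d² takes of 4.45² = 19.8. The imbalance and the lost precision are one quantity seen from two sides and should not be added together.

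**Step 4: bias and type I error.** The ANCOVA was simulated with and without the withdrawal indicator: 4,000 runs, p = 0.5, d = 2, SD 4.45, 86 per arm, center effect left out.

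| True effect | Mean estimate, omitted | Mean estimate, included | Rejection, omitted | Rejection, included |
|---|---|---|---|---|
| 0 | 0.01 | 0.01 | 4.9% | 4.8% |
| 1.9 | 1.90 | 1.91 | 76.6% | 78.9% |

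The estimate is unbiased either way and the test keeps its level. Only power moves.

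**The case against.** A reader might infer that withdrawal drift is mixed into the estimated treatment effect. The documents do not support that. Randomization follows the baseline evaluation, so controller history is settled before allocation. Both arms have the same as-needed drugs. Drift is then balanced in expectation and cancels in the between-arm contrast, which is what the primary model estimates; the simulation agrees.

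The case against acting goes further:

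- Baseline score, treatment and center make a standard, valid ANCOVA, and many other baseline factors could be proposed. That is true, and the model is not in error. Prior controller use differs from a generic covariate because the entry criteria themselves create the two groups.
- The ordinary standard error already allows for chance imbalance. This stands: the shift in Step 3 is part of normal sampling error, not an uncorrected distortion.
- The gain is small and rests on assumed inputs. The top of the range needs a 3-point drift, larger than the 1.9-point target difference. The 1.6-point improvement anticipated under sham shows no net deterioration, although it cannot exclude drift in a subgroup. This stands and limits the weight of the point.
- An article may leave controller washout and stratification to the full protocol. Agreed, and their absence is not the finding. The model terms, by contrast, are stated in full.
- A yes/no covariate does not capture how recently the drug was stopped. This stands in part. Counting use stopped in order to enter avoids coding such patients as never treated, but the adjustment remains coarse.
- The article names its comparison openly and nowhere says the result extends to patients on controllers. That is fair. A scope sentence is still useful, because the Background motivates acupuncture as an adjunct to conventional management.

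**Conclusion.** The point holds as one of precision and interpretation, not of bias. The primary model omits a plausible prognostic factor that is fixed before randomization and needed to apply the entry criteria. The verum-sham difference stays unbiased and type I error stays at about 5%. The cost is about 0.4 to 4.4 points of power, with 87 to 96 per arm needed for 80% in place of 86, and a chance imbalance that goes unadjusted. The sample size aims at exactly 80%, and the step to 100 is reserved for dropout, so no stated margin is set aside for this.

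These sizes rest on an assumed 30% to 70% withdrawn, an assumed drift of 1 to 3 points, and an SD of 4.45 inferred from the sample size. If withdrawal causes little drift within 6 weeks, almost nothing is lost.

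Within-arm changes, including the anticipated 3.5 and 1.6 points, may include drift and cannot be read as benefit. The no-bias conclusion concerns the omitted term only. Dropout that differs by arm combined with LOCF would be a separate matter, and a covariate alone would not cure it.

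**What to change.** - Add prior controller use to the primary ANCOVA as a pre-specified fixed covariate (yes/no). Define it as use established at screening, including use stopped in order to enter the trial. Specify it before unblinding, because adjustment chosen after an imbalance is seen looks post hoc.
- Base conclusions on the verum-sham difference, and do not interpret within-arm ACT changes as treatment benefit.
- State in the report that the result applies to acupuncture plus as-needed salbutamol and/or prednisone without controllers, not to acupuncture added to controller therapy.

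The cost is one degree of freedom, a variable that eligibility screening already needs, and a sentence or two of text. No extra patients or visits are needed. No washout or other clinical rule is proposed.
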